**Figure 1 F1:**
[figure not shown]
Conceptual framework underpinning the Lively Minds intervention. KG, kindergarten; PS, play schemes.

The programme is owned and implemented by the Ghana GES. This is a key difference between the version of the programme evaluated in the efficacy trial and the current version. At that time, the programme was owned by the NGO Lively Minds who engaged the GES in implementation but remained in the driving seat throughout, retaining control over programme content and implementation strategy and leading on all aspects of programme implementation and monitoring on the ground. Control and responsibility for all of these elements have now been transferred to GES. Lively Minds provides technical assistance; for example, it helps districts set up the necessary monitoring and accounting databases, attends key training sessions of district teams and KG teachers, responds to queries from the GES Working Group in charge of the programme and accompanies the district officials to some of the monitoring visits.

Implementation is conducted at the district level, that is, once a district is enrolled in the programme, all of the KGs in the district are invited to participate. Before enrolment of districts begins, NGO Lively Minds familiarises the regional GES office (there are currently 16 regions in Ghana made up of 261 districts) with the Lively Minds Programme and trains a team tasked with mobilisation of the districts. Following this, there are five main implementation stages starting from enrolment of the district into the programme. These are summarised in figure 2. Online supplemental material S1 provides a more detailed explanation of what each step entails.

10.1136/bmjopen-2022-061571.supp1Supplementary data

**Figure 2 F2:**
[figure not shown]
GES Lively Minds (LM) implementation model. GES, Ghana Education Service; PS, play schemes; PTA, Parent Teacher Association; KG, kindergarten.

### Trial design

This study is an open-label CRCT, accommodating the phased and complete roll-out of the GES-LM Programme. The programme will be scaled to all of Northern Ghana’s 60 districts over 10 phases; each phase (equivalent to one school term) covering a district group (DG) of six districts, from September 2021 to September 2024 (figure 3A). Researchers at the the Institute for Fiscal Studies (IFS) randomised districts to DGs using R V.4.1.1. DGs will be enrolled into the evaluation study from January 2022 to September 2024 (hence, leaving out DG1) in six evaluation cohorts (ECs) (figure 3B). In each EC, one DG is allocated at random into the treatment group and one to the control DG. DG6 and DG7 are used first as control and later as treatment DGs, relying on different cohorts of children (those starting school in 2022 and those in 2023) (in different schools). DG10 will provide the control group for EC5 and EC6 using different schools. Control DGs will begin to receive the programme three terms after being enrolled into the study, after endline data collection has been completed (with the exception of EC6, where control will receive the programme after two terms). Baseline data collection will start at the end of January 2022 (after participant enrolment) (figure 3C). Data collection will proceed continuously through to the end of the project in early 2025. Figure 4 shows this design in a flow diagram, while figure 5 shows the participant timeline.

**Figure 3 F3:**
[figure not shown]
Project design: (A) intervention roll-out; (B) treatment and control allocation and cohort selection; (C) baseline and endline data collection timing. DG, district group; EC, evaluation cohort.

**Figure 4 F4:**
[figure not shown]
Randomisation flow diagram. EC, evaluation cohort.

**Figure 5 F5:**
[figure not shown]
Participant timeline.

### Sample size and sampling

Within each district, we plan to randomly sample five programme-eligible preschools (excluding efficacy trial schools) and eight children who are enrolled or about to enrol in the sampled preschool. In DG6, DG7 and DG10, we will sample children and schools twice (once for each cohort of children). When we sample for a second time, we will exclude schools previously enrolled into the study. This gives us a minimum total sample of 360 preschools and 2880 children and households.

Schools will be selected at random from a complete school list in each district provided by the GES. We will exclude focus on government schools, and exclude atypical schools, specifically only boys’ and only girls’ schools (more than 99% of government schools are mixed gender), as well as schools with less than 20 enrolled students. Doing so, we exclude 20 schools from the sampling frame (20 small ones, one of which has no boys enrolled in KG).

Our study participants will be children and their households, who attend or are due to attend KG. These will be identified from school enrolment lists, except for EC1 where due to the COVID-19 pandemic, school openings were different and lists were not readily available. We therefore sampled in this EC only from a census surrounding the school. To be eligible for the study, children must fulfil both of the following criteria (the same as in the efficacy trial):

Be aged between 3 and 5 years.Be enrolled or planning to enrol in the sample preschool in the coming term.

Where more than one child is eligible within a single household, we will randomly select one child to be a part of the study. Primary caregivers (PCGs) will be asked for their consent (and to give consent on behalf of their child) before being enrolled in the study. Model consent form and information sheet for PCGs are provided in online supplemental materials S2 and S3.

### Outcomes

In each sampled unit (school), we intend to conduct four separate surveys/assessments types, each to be implemented both at baseline and at endline, two to three school terms later. Surveys/assessments include: (1) child assessment, (2) PCG interview, (3) KG teacher interview and classroom observation, (4) community survey. These surveys will be collected by local well-trained and experienced interviewers, who will not be informed about treatment allocation.

In order to gather evidence on district-level preparedness for the programme (for later heterogeneity analyses), we additionally plan to conduct a survey of the district official in charge of preschool programmes in each district once. We will also collect secondary data available on districts, such as languages spoken or voter turnout.

We have three sets of primary outcomes:

Child cognitive development measured using the International Development and Early Learning Assessment (IDELA) tool^22^ and tasks from the Harvard Laboratory for Development Studies, all previously used in Ghana.Child socioemotional development measured using Strengths and Difficulties Questionnaire^23 24^ administered to the PCG.Child health measured using height/weight for age and height-for-weight Z scores, following WHO guidelines.

Our secondary outcomes are as follows:

Maternal mental health, measured used the Kessler-10 and Warwick Edinburgh Mental Wellbeing Scale and knowledge of ECCE practices.Teacher knowledge, motivation and teaching quality, measured using classroom observation.Parental investment measured through quality in the home environment (Family Care Index (FCI) and Home Observation Measurement of the Environment) and the quality of the parent–child relationship (Child–Parent Relationship Scale).WASH practices in the home (eg, handwashing practices, toilet facilities, open defecation practices).Acute malnutrition measured using middle upper arm circumference. Beyond being of interest in its own right, this is the health outcome used in the efficacy trial,^25^ which will allow us to compare outcomes across both trials.

In selecting measures for our key outcomes, we prioritised those which have already been validated and used in the study context (for example, IDELA^22 26^) or in a context that is similar. Since very little related work has been conducted in our study context, this was not possible for all outcomes that we want to capture. For these outcomes, we next identified measures which have been widely used and validated across multiple contexts, for example, the Kessler-10 and FCI. We will adapt these measures to the study context following best practice^27^: tools will be reviewed for sociocultural relevance and linguistic accuracy through consultation with local professionals and modified accordingly; tools will be translated and back-translated into all of the main languages spoken in the study communities. Full validation of the tools before administration of the baseline is beyond the scope of this study. However, all outcome measurement tools will be piloted on small samples in the study area, feedback on performance will be collected from the surveyors and further adaptations will be made. As part of the training, the survey team will be required to achieve inter-rater reliability of at least 0.8 (κ statistic) on the child assessment and classroom observation tools. Once data are collected, we will assess reliability and validity of the outcome measures by examining whether any items have a lot of missing responses, items show sufficient variability, correlations with other variables go in the expected direction and measures exhibit sufficient degree of internal consistency (Cronbach’s α of at least 0.7). We will also assess dimensionality of the measures using exploratory and confirmatory factor analysis and functioning of individual items using Item Response Theory to generate item characteristics curves. More detailed information on these outcomes is provided in online supplemental material S4.

### Data management protocols and data statement

For details on data management, please refer to the project’s management registration: https://ifs.org.uk/uploads/Research registraion form.pdf. Data availability is outlined in online supplemental material S5.

### Sample size and power

As our design does not deviate in a substantive way from a conventional two-arm CRCT, we use standard CRCT methods to assess statistical power. For the power analysis, we consider the district as a cluster, providing us with 54 clusters. We consider the full sample size of 2,880 children (5 school per district-cohort, 8 children per school). We leverage data available from the efficacy trial to better inform how covariates increase our power to detect effects, including expected loss to follow-up, which we set at 6%.

We calculate minimum detectable effects (MDEs) using the following formula^28^:

(1)
$$MDE={\left(\frac{{\left(t_{\frac{\alpha }{2}}+t_{\beta }\right)}^{2}\sigma^{2}(m\rho \left(1-R_{c}^{2}\right)+\left(1-\rho \right)\left(1-R_{p}^{2}\right)}{n}\right)}^{\frac{1}{2}}$$

α denotes the significance level, β power, ρ unconditional intracluster correlation (ICC), *t* is the critical value of the t-distribution, σ is the SD of the outcome, *n* is children per arm, *m* is children per cluster, $R_{c}^{2}$ is proportion of cluster-level variance component explained by covariates and $R_{p}^{2}$ is the individual equivalent. One can interpret the effect of $R_{c}^{2}$ and $R_{p}^{2}$ as altering the ‘variance inflation factor’ of the power calculation—when they equal zero, the formula reduces to the standard CRCT one. We set α to 0.05, β to 0.8.

We estimate the ICC for each outcome data using data from the efficacy trial (ranging from 0.011 to 0.110). Note that we cannot conduct the same exercise for all of our primary outcomes, as some were not included in the original trial. The MDEs for some of our primary and secondary outcomes measured at the child/household level are shown in table 1. The power to detect effects at the school level is significantly more limited.

**Table 1 T1:** Minimum detectable effects (MDEs)

Outcome	MDE
Cognition factor score	0.110
Middle upper arm circumference	0.137
Knowledge Infant Development Index	0.119
Family Care Index	0.210
Parent–child interaction (Child–Parent Relationship Scale)	0.126

Each outcome controls for its baseline value only.

The MDE for the cognition score will allow us to determine whether the scaled up, government-owned and run version of the Lively Minds Programme is at least as effective as the NGO-run smaller scale version evaluated in the efficacy trial in its key aim of improving cognitive development of preschool children. However, if the scale-up results in a significant reduction in effectiveness, we will not be able to determine whether the programme continues to have an impact. It should be noted that efficacy trial impacts were largest for the poorer children in the sample. On average, the areas where the scale-up is happening are poorer than those where the efficacy trial took place, so even if there is some loss of effectiveness as the result of the scale-up, we should still be able to detect impacts given our power.

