### Objectives

The project’s key research questions are as follows:

What is the impact of the GES-LM at scale on child development?How does the impact of the intervention vary by child, teacher, classroom/school and district characteristics?What role do intervention fidelity and compliance play (intensity of training, dosage, hygiene promotion, quality of play sessions, supervision by teachers and district education offices) and how can the design be adapted to maximise cost-effectiveness?Are impacts achieved through changes within the classroom/school and/or the children’s home environments, including teacher and parent behaviour?

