### Analysis plan

#### Intention to treat

For our primary and secondary outcomes, we will estimate an intent-to-treat effect of the programme. Our design is the same as a CRCT stratified by EC. As such, we follow the standard estimation technique for two-way stratified CRCTs, For the outcome variable *Y* of individual *i* in district *j* at date *t,* we estimate the following:

$$Y_{ijt}=\mu +\gamma_{t}+\theta Treatment_{ijt}+\beta X_{ijt}+\varepsilon_{ij}$$

Where $\gamma_{t}$ is an evaluation cohort fixed effect, $Treatment_{ijt}$ is binary indicator variable equal to 1 if individual *i* is in a treatment district at date *t*, $X_{ijt}$ is a set of control variables. The treatment effect we identify is θ, and SEs will be clustered at the school level.

We will compute the Romano-Wolf stepdown p values to adjust for multiple hypothesis testing. Hypotheses will be arranged within families of outcomes—that is, each set of research questions separately.

The set of controls $X_{ijt}$ will be identified using a double-lasso procedure of the covariates we collect as part of our data collection. We will present estimates of the treatment effect both with and without these control variables. In addition to those controls that the double-lasso procedure generates, we will use (at a minimum) the following controls:

Mother’s age (quadratically).Mother’s educational attainment.Tester fixed effects (where relevant).Time between baseline and endline measurements.Child’s age.Child’s sex at birth.Baseline value of the outcome variable of interest.

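### The Table 1 MDEs carry 80% power only for unadjusted tests, while the planned inference adjusts p values by Romano-Wolf, and the cognition MDE is relied on without that caveat

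*Protocol article*

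**What the plan says.** Protocol article, Sample size and power: the MDE formula uses the critical value at α/2 plus the value for power, and "We set α to 0.05, β to 0.8" (the 0.8 is the power). Table 1 gives one MDE per outcome, cognition being 0.110, with adjustment for the baseline value only. No allowance for multiplicity is mentioned. The paragraph after the table says that the cognition MDE lets the trial establish whether the scaled programme is at least as effective as the efficacy-trial version. It concedes that, if effectiveness falls markedly, the trial could not tell whether an impact remains.

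Analysis plan, Intention to treat: "We will compute the Romano-Wolf stepdown p values to adjust for multiple hypothesis testing". The grouping is: "Hypotheses will be arranged within families of outcomes—that is, each set of research questions separately". No list of families or count of hypotheses is given.

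Outcomes: "We have three sets of primary outcomes", namely cognitive development, socioemotional development and health, with health measured by several Z scores. Objectives: the first research question is "What is the impact of the GES-LM at scale on child development", which covers all three sets.

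**The concern.** The MDE is the effect that a stated test detects with stated power. Here that test is a single comparison at 5%, whereas the analysis plan applies a stepdown adjustment across a family. In a family of two or more imperfectly correlated hypotheses, the first step needs a larger critical value than a single test does. An effect equal to the tabulated MDE then has less than 80% power on its adjusted p value, unless the other members of the family are almost certain to be rejected.

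This bears on the cognition row in particular. Of the five rows in Table 1, only cognition is a primary outcome, and it is the figure from which the protocol draws its conclusion about what the trial can show. By the authors' own account the margin is limited, so a reader should know which test the 0.110 belongs to.

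**Working it through.** **Inputs from the protocol article.** Two-sided α = 0.05, power 0.80, cognition MDE 0.110 (Sample size and power, Table 1); "we consider the district as a cluster, providing us with 54 clusters"; three primary outcome sets (Outcomes).

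**Assumptions.** Degrees of freedom 54 − 2 = 52. K, the number of hypotheses in the family, is not stated:
- K = 3 takes one hypothesis per primary set under the first research question.
- K = 5 counts cognition, socioemotional development and three health Z scores separately.
- K = 2 is shown as the smallest case in which adjustment matters.

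**Step 1: the plan's own figure.** Table 1 cannot be recomputed row by row, because outcome-specific ICCs and R² values are not given. It need not be. In the MDE formula every other term multiplies the sum t(α/2) + t(β), so the ratio of adjusted to unadjusted MDE depends on the critical values alone. On 52 df the sum is 2.007 + 0.849 = 2.855. An effect at its MDE is thus 2.855 standard errors from zero, and power against the critical value 2.007 is 80%, as the protocol intends.

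**Step 2: Bonferroni bound.** Replace 2.007 by c = t(1 − 0.025/K, 52). The adjusted MDE is 0.110 × (c + 0.849)/2.855. Power at 0.110 comes from the noncentral t with noncentrality 2.855.

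| K | c | MDE ratio | Cognition MDE | Power at 0.110 |
|---|---|---|---|---|
| 1 | 2.007 | 1.000 | 0.110 | 80% |
| 2 | 2.308 | 1.106 | 0.122 | 71% |
| 3 | 2.474 | 1.164 | 0.128 | 65% |
| 5 | 2.674 | 1.234 | 0.136 | 57% |

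These are worst-case values. Romano-Wolf uses the correlation between the statistics and relaxes the threshold after each rejection.

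**Step 3: stepdown with correlation.** A stepdown procedure on the maximum absolute Z was simulated under a normal approximation, where an effect at its MDE lies 1.960 + 0.842 = 2.80 standard errors from zero. The common correlation was set to 0, 0.3, 0.5 and 0.8. The table gives power for cognition at its MDE across those correlations.

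| K | Others null | All at their MDE |
|---|---|---|
| 2 | 72–74% | 77% |
| 3 | 66–71% | 74–75% |
| 5 | 59–67% | 70–72% |

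For K = 3 the first-step critical value runs from 2.39 (correlation 0) down to about 2.25 (correlation 0.8), against 1.96 for a single test. If the other members are certain to be rejected, power returns to 80%.

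**Step 4: could the extra covariates offset this?** Table 1 adjusts for baseline only, while the analysis plan adds further controls. To cancel the K = 3 Bonferroni step, residual variance would have to fall by 1 − 1/1.164² = 0.26, or about 26%. The reduction needed under Romano-Wolf is smaller. The protocol claims neither.

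**The case against.** The strongest reply is that no stated figure is wrong. The protocol says openly that α is 0.05, describes a per-outcome calculation, and never claims 80% power under family-wise adjustment. That is correct, and it rules out one tempting inference: that Table 1 contains an arithmetic error. The documents do not support that, since 80% holds for the unadjusted tests that the formula describes.

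A second reply is that the protocol promises only to compute adjusted p values and does not say that conclusions rest on them alone. This also stands as far as it goes. But adjustment is the only multiplicity rule given, and the text after Table 1 does not confine its claim to unadjusted tests.

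Third, the family is inferred. The primary outcomes are called three sets, so cognition might form a family of its own, and then nothing is lost. Grouping by research question points the other way, because the first question covers all child outcomes. The number of hypotheses may properly be left to the statistical analysis plan, so its absence here is not the point. The mismatch lies between two things that the protocol does state.

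Fourth, the Bonferroni figures overstate the loss. This is accepted: they are given only as a bound, and the simulated values are the better guide.

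Finally, a reader might infer that the conclusion about matching the efficacy trial fails. The documents do not support that either. The efficacy-trial effect is not given, so nobody can tell from the text whether an MDE of 0.122 or 0.128 would change the statement.

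**Conclusion.** The point holds as a mismatch between the basis of the power calculation and the planned inference. With K = 3 assumed, 80% power at the cognition MDE becomes about 66–71% if the other two effects are null and 74–75% if all sit at their MDE. The MDE that keeps 80% power lies between 0.110 and a bound of about 0.128.

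The direction follows from the text for any family of two or more imperfectly correlated hypotheses, unless the others are almost certain to be rejected. The size rests on assumed values of K and correlation, on 52 df for the bound, and on a normal approximation for the simulation. The quantified claim is limited to cognition, because the other four rows of Table 1 are not primary outcomes and their families cannot be identified from the protocol. The issue is moderate: it calls for a correction to a figure that is relied on, not for a redesign.

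**What to change.** - Label Table 1 as unadjusted for multiplicity.
- Add the family-adjusted MDE for the primary cognition outcome, using a simulated Romano-Wolf critical value for the intended family and the Bonferroni value as the upper bound. Give the family assumed.
- In the paragraph after Table 1, either base the statement about cognition on the adjusted figure or say that it applies to the unadjusted test.

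The cost is a column or footnote, a short simulation and one reworded sentence. The stated MDE becomes somewhat less favourable. Sample size, data collection and the analysis itself stay as they are.

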In 2017/2018, [name] and SK led an efficacy trial of Lively Minds—a holistic ECCE programme which engages parents and preschools to achieve healthy child development of children 3–5 years old in rural Ghana and promotes inclusion of children with disabilities. The trial revealed a positive impact on child health, as well as cognitive and socioemotional development, partly mediated by improvements in parenting practices.^11^

As a result of this evidence, the Ghana Education Service (GES) plans to integrate the Lively Minds Programme with core instruction across all preschools in Northern Ghana over the next 4 years aiming to cover over 4000 preschools, reaching 1.3 million children, reducing costs to $7 per child per year (less than one-third of the original cost, and significantly below typical group parenting programme costs in LMICs, estimated to be US$30–US$35 per child).^12^ Ownership of the programme has been transferred from the non-governmental organisation (NGO) that developed it to GES. We will therefore refer to the programme as the GES Lively Minds (GES-LM) Programme.

This study is a cluster randomised controlled trial (CRCT) evaluating this scale-up, with randomisation achieved through randomisation of the order in which districts begin to receive the programme. We will assess whether the impacts found at efficacy trial stage are sustained and investigate key mechanisms underlying these in order to determine how implementation and cost-effectiveness could be further improved.

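### The cognition MDE of 0.110 is an effect detectable against zero, so it cannot show that the scaled programme is at least as effective as the NGO-run version

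*Protocol article*

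**What the plan says.** The Introduction of the protocol article sets the aim: "We will assess whether the impacts found at efficacy trial stage are sustained".

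Under Sample size and power, the MDEs come from a standard two-arm cluster-trial formula, with "We set α to 0.05, β to 0.8" (β here denotes power). On clusters, "we consider the district as a cluster, providing us with 54 clusters". On sample size, "We consider the full sample size of 2,880 children (5 school per district-cohort, 8 children per school"). Table 1 gives "Cognition factor score 0.110".

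The text after the table says this MDE will let the team determine whether the government-run programme "is at least as effective as the NGO-run smaller scale version evaluated in the efficacy trial in its key aim", namely preschool children's cognitive development. Two qualifications follow. The first is that "if the scale-up results in a significant reduction in effectiveness, we will not be able to determine whether the programme continues" to have an effect. The second, resting on the scale-up areas being poorer and the earlier effects being largest in poorer children, is that "even if there is some loss of effectiveness as the result of the scale-up, we should still be able to detect impacts".

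The Analysis plan (Intention to treat) estimates a single treatment effect θ. Under Trial design, the controls are districts that have not yet received the programme. There is no NGO-run arm.

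**The concern.** Detecting an effect against zero and showing an effect at least as large as an earlier one are different hypotheses. The second needs the earlier estimate as a benchmark, a tolerated loss, and the uncertainty of both estimates. An MDE against zero supplies none of these.

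At stake is what the trial may conclude about whether the efficacy-trial impacts held up at scale. The protocol credits the design with a capability that its own figure does not give it. A reader relying on that sentence could take a significant θ as evidence of full retention, or a non-significant θ as evidence of loss. Neither follows. The estimate of θ itself is unaffected.

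**Working it through.** **Inputs.** From Sample size and power: MDE 0.110 (taken as SD units, since Table 1 gives none), two-sided α 0.05, power 0.80, 2,880 children (1,440 per arm at 1:1), 6% loss to follow-up (about 1,354 per arm), and ICCs from 0.011 to 0.110 across outcomes. The ICC and R² for cognition are not given. The efficacy-trial effect E and its SE are not given either, so values for them below are assumptions.

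**The plan's figure.** Without the cognition ICC and R², 0.110 cannot be reproduced uniquely, but it is attainable. With n = 1,354, m = 40, ICC 0.05 and a common R² of 0.3, the formula as printed gives √[2.8016² × (40×0.05×0.7 + 0.95×0.7)/1,354] = 0.109. With ICC 0.011, R² 0.3 and the factor 2 of the usual two-arm variance, it gives 0.108. I therefore take 0.110 as stated.

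**Implied precision.**
- SE = MDE/(z₀.₉₇₅ + z₀.₈₀) = 0.110/(1.960 + 0.842) = 0.0393.
- 95% CI half-width = 1.96 × 0.0393 = 0.077.
- An estimate of about 0.077 or more is therefore significant, and significance excludes only zero and below.

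**Showing an effect of at least E.** Treat E as a fixed known number. If θ = E, P(lower 95% limit > E) = 1 − Φ(1.96) = 2.5%. This holds for any E and any SE. For 80% power to show θ > E, the true effect would have to be E + 0.110.

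**Power against zero after a loss.** With a fraction f of E retained, power = Φ(fE/0.0393 − 1.96). Power to exclude a 50% loss when θ = E is Φ(0.5E/0.0393 − 1.96), the same expression as power against zero at f = 0.5, so one column serves both. The last column holds the margin at 0.5E and gives the efficacy estimate an assumed SE of 0.05, so the SE of the difference is √(0.0393² + 0.05²) = 0.0636.

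| Assumed E (SD) | Power vs zero, no loss | 25% loss | 50% loss (also: power to exclude a 50% loss if θ = E) | Excluding a 50% loss, efficacy SE 0.05 |
|---|---|---|---|---|
| 0.10 | 72% | 48% | 25% | 12% |
| 0.11 | 80% | 56% | 29% | 14% |
| 0.15 | 97% | 82% | 48% | 22% |
| 0.20 | 99.9% | 97% | 72% | 35% |

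At E = 0.20, a programme that had lost half its effect would still be significant 72% of the time. Conversely, at a true effect of 0.110 the test misses 20% of the time.

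**Difference between trials.** With an assumed efficacy-trial SE of 0.03 to 0.06, the minimum detectable difference is 2.80 × √(0.0393² + SE²) = 0.138 to 0.201.

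**The case against.** The best defence is that the sentence sits in a power section and probably means that the trial can detect, against zero, an effect as large as the efficacy trial's. The qualification about a significant reduction fits that meaning. I accept this as the likely intention, but the sentence claims more.

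Four stronger readings are tempting, and the document does not support them.

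- A reader might infer that the paragraph contradicts itself. It does not. A significant reduction and some loss are different sizes of loss, and both statements can be true. The weakness is that neither is quantified.
- A reader might infer that the reassurance about some loss is false. That cannot be shown. At an efficacy effect of 0.15 or 0.20, power against zero after a 25% loss is 82% or 97%. At 0.10 or 0.11 it is 48% or 56%. The document does not say which case applies.
- A reader might infer that p < 0.05 will be reported as equal effectiveness. No passage sets such a rule, and the first research question, on impact at scale, is answered by θ against control.
- A reader might count the missing margin or cross-trial test as an error. It may stand in an analysis plan that is not shown. The Outcomes section already intends a comparison across trials for arm circumference. The point here is a capability asserted from the wrong quantity.

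It is also fair that the back-calculated SE need not be the analysis SE. The MDE adjusts for the baseline outcome only, whereas the analysis adds further controls and clusters SEs by school. The 2.5% result does not depend on the SE.

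**Conclusion.** The claim is wrong as written. An MDE of 0.110 against zero does not let the trial determine whether the scaled programme is at least as effective as the NGO-run one.

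The central result, a 2.5% chance of the lower limit exceeding the efficacy effect when the two are equal, needs only that the efficacy effect be treated as fixed. The power to exclude a 50% loss, 25% to 72%, rests on assumed efficacy effects of 0.10 to 0.20 SD and an SE of about 0.039. It is below 80% throughout that range, and lower once the efficacy estimate's own SE is counted.

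Sample size, estimator and primary test are untouched. This is a correction of a stated capability and of what may be concluded about sustained impact. It is worth making but is not a flaw in the trial's main comparison.

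**What to change.** 1. Replace the sentence with a statement that the trial has 80% power to detect an effect of 0.110 SD on the cognition score against zero.
2. In place of the unquantified reassurance about some loss, give power against zero at stated fractions of the actual efficacy estimate, for example after losses of 10%, 25% and 50%.
3. For the question of sustained impact, report the difference between θ and the efficacy estimate on the same cognition score, with a CI carrying both SEs. State that the comparison is not randomised: the scale-up areas are poorer, so a population difference could offset or mimic a change in programme effect.

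The cost is a few lines of wording and one extra analysis, using efficacy-trial data the team already draws on for its power calculation. The stated capability becomes less favourable.
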